### 5.3. Prohibited Medications or Precautions

#### June 13, 2003 – Amendment 4

The following medications are not be taken at any time during this study:

- Lipid-regulating drugs not specified as study treatment in the protocol: probucol, fibrates and derivatives, bile-acid sequestering resins, other HMG-CoA reductase inhibitors, niacin (>500 mg/day), and supplemental fish oils (prescription only). HMG-CoA reductase inhibitors may only be taken as described in the protocol. ***Following the completion of year 1, patients will be allowed to utilize certain lipid-regulating drugs ("add-on therapy") if the patient's LDL levels are found to be higher than protocol range (see section 6.4.1). "Add-on" therapy will be agreed upon by investigator and Pfizer medical personnel or designee.***
- Patients taking a lipid-regulating drug(s) must have the medication discontinued at or prior to the screening visit to be eligible for screening, except in the case of probucol where medication must have been discontinued for at least 12 months.

The following medications should not be administered concurrently with study drug.

- Any immunosuppressive agent (e.g., cyclosporin).

- Other drugs known to be associated with an increased risk of rhabdomyolysis in combination with HMG-CoA reductase inhibitors [including: erythromycin, clarithromycin, any chronic systemic antifungal use, mibefradil dihydrochloride, nefazodone, fluvoxamine and other potent inhibitors of cytochrome P450-3A4]. Coadministration of atorvastatin (10 mg) and azithromycin (500 mg QD) has been shown not to alter plasma concentrations of atorvastatin.

Should these medications be necessary during the course of the trial, consideration should be given to temporarily withholding study drug and restarting it only after time has elapsed to allow for sufficient clearance of the medication. In addition, temporarily withholding study drug should be considered in any patient with a risk factor predisposing to the development of renal failure secondary to rhabdomyolysis, including severe acute infection; hypotension; major surgery; trauma; severe metabolic, endocrine, or electrolyte disorders; and uncontrolled seizures.

A list of the commonly prescribed medications discussed above may be found in Appendix B.

As co-administration of atorvastatin (80 mg) and digoxin increased steady-state plasma digoxin concentrations by approximately 20%, patients taking digoxin should be monitored appropriately.

While atorvastatin had no clinically significant effect on prothrombin time when administered to patients receiving chronic warfarin therapy, prothrombin time should be monitored as clinically appropriate.

#### 5.4 Allowable Concurrent Medications

The dosage and regimen of any chronic, permitted concurrent medications (e.g., calcium channel blockers, b-blockers, hormone replacement therapy, hormone contraceptives, thiazides, loop diuretics, H-2 antagonists, aspirin, phenytoin) should be stabilized (for at least 30 days) before the open-label run-in phase begins (Visit 2) and kept constant (as is medically appropriate) throughout the study. Any medications prescribed chronically or intermittently during the study must be reported on the concurrent medication Case Report Form (CRF). The occasional (< 3 times per week) use of antacids is permitted.

## 6. STUDY DESIGN AND METHODOLOGY

### June 13, 2003 – Amendment 4

#### 6.1. Study Design

This is a double-blind, randomized, parallel-group study of the recurrence of **cardiovascular events** in patients whose LDL-C will be lowered on average to approximately 100 mg/dl (2.6 mmol/l) compared with those whose LDL-C is approximately 25% lower. Patients will have clinically evident CHD. Following dietary therapy, all patients meeting initial eligibility criteria will begin an open-label atorvastatin 10 mg (once daily) run-in period. Patients whose LDL-C is < 130 mg/dl (< 3.4 mmol/l) at the end of the run-in period (average of Visits 3 and 4) and meet all other inclusion/exclusion criteria will be randomized to double-blind therapy consisting of either atorvastatin 10 mg/day or 80 mg/day. Treatment and follow-up of patients will be continued until ~~letter, sentence, paragraph deleted~~ the number of **major coronary**

*events (CHD death, non-fatal myocardial infarction, or resuscitated cardiac arrest)* reaches 750 (*approximately 5.5 years average follow-up*). Early stopping rules may be applied based on interim analyses.

## **6.2. Study Schedule and Guidelines For Visits**

A study timetable and the specific procedures to be performed at each visit are shown in Appendix A. However, a patient may be seen at any time for reasons of safety. All laboratory procedures such as clinical laboratory measurements and lipoprotein determinations will be performed by a central laboratory.

The timing of clinic visits should be consistent throughout the study and the study medication should be taken at approximately the same time each day. When laboratory determinations are required for a scheduled study visit, blood draws must occur after a minimum 12-hour fast (water allowed). If this is not possible, the visit must be rescheduled in a timeframe to allow for continuous dosing of study drug (~10-20 days dependent on study period and visit interval). Patients should have been generally compliant with study medication in the two week period prior to a clinic visit. If a patient has not been compliant or has been temporarily discontinued from medication, the clinic visit is to be rescheduled to allow for a two week period on study medication.

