#### **6.2.4 Double-Blind Active Treatment Period**

This period begins at Visit 5 (Week 0). Procedures performed at this visit include an assessment of vital signs, an ECG and physical exam, repeat clinical chemistry/fasting lipid determinations and continued dietary counseling. The ECG and physical exam may be performed between Visits 4 and 5 once a patient's lipid levels qualify them for randomization.

The open-label atorvastatin 10 mg therapy will stop at Visit 5. Qualified patients will be randomized to 1 of 2 blinded treatment groups, either 80 mg atorvastatin or 10 mg atorvastatin. The patient should take the study medication once daily. Neither the investigator nor the study sponsor will be informed of the lipid values of randomized patients (except as noted in section 6.4.1) in order to maintain the blind of the study.

Visits will be at designated intervals during the active treatment period. Patients will be regularly counseled on following the NCEP Step I, Step II (see Appendix A.3) or equivalent diet in order to maintain body weight, and lipid levels. Other procedures such as lipid profiles, clinical laboratory measurements, physical examinations, and electrocardiograms will be performed according to the timetable in Appendix A. Patients will be assessed for the occurrence of adverse events and the change or addition of concomitant therapies at all visits in the double-blind treatment period. Medical resource utilization regarding all hospitalizations and revascularization procedures will be collected.

During the first year of the double-blind period, four follow-up visits are scheduled at weeks 12 and months 6, 9 and 12.

After completion of the first year of active treatment, patients are to have scheduled study visits every six months. At each visit, vital signs, clinical end points, adverse event, and concurrent medication information will be collected. On alternating visits (i.e., annually) in addition to the above, physical examinations and electrocardiograms will be performed and laboratory specimens will be collected.

While on average a patient will be on active treatment for 5 years, the actual length of time for an individual patient will vary based on the study recruitment rate, primary event rate and when the patient was recruited relative to the entire study cohort. Therefore, it is estimated that actual active treatment for a patient could range from approximately 3 to 7 years.

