#### **June 13, 2003 – Amendment 4**

#### **6.6 Patient Follow-up/Discontinuation of Study Drug**

Every effort within the bounds of safety and patient choice should be made to have patients complete the study while remaining on study drug. Regardless of their study drug status, all randomized patients should be followed for clinical end points until study completion. Patients are not to be withdrawn from the study drug or followup if they experience a non-fatal clinical end point.

Once randomized, patients should not be discontinued from study drug for noncompliance; they should, however, be counseled on the importance of regularly taking their medication. In general, patients will be encouraged to complete the study and its follow-up for clinical end points, although they may withdraw at any time without prejudice.

Consideration should be given to temporarily withholding or discontinuing the study

drug in any patient with a risk factor or concomitant medication predisposing to the development of renal failure secondary to rhabdomyolysis, including severe acute infection, hypotension, major surgery, trauma, severe metabolic, endocrine, or electrolyte disorders, and uncontrolled seizures.

If a patient becomes pregnant during the trial, study drug should be discontinued and the patient apprised of the potential hazard to the fetus.

Patients prematurely discontinued from study drug during the double-blind phase should have all end-of-study procedures performed (see annual visits beginning at month 24) and may then return to non-protocol lipid therapy. If the final lipid measurements (lipid profile) cannot be performed within 3 days of the cessation of therapy, these measurements should not be performed at all. In this case, the previously determined lipid values will be carried forward for the purpose of analysis.

For patients who withdraw from the double-blind period early, an effort will be made to collect full follow-up information on primary and secondary clinical end points until such time that the study is completed. Methods of follow-up for these patients should include clinic visits when possible according to the timetable (Appendix A) but telephone or mail follow-up should be attempted as well when visits are not possible.

If necessary, an independent search firm will be contracted to locate patients who are lost-to-follow-up at the end of the study to determine if the patient is alive or deceased.

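### Section 6.2 postpones the whole clinic visit when a patient is non-compliant or temporarily off study drug, so routine ascertainment after randomization depends on adherence, in conflict with Section 6.6

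*Supplement*

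**What the plan says.** The general visit guidelines in Section 6.2 set a condition on attendance: "Patients should have been generally compliant with study medication in the two week period prior to a clinic visit". If the patient has fallen short, or "has been temporarily discontinued from medication, the clinic visit is to be rescheduled to allow for a two week period on study medication". The same section allows extra contact: "However, a patient may be seen at any time for reasons of safety".

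Section 6.2.4 sets out what the double-blind visits are for. "After completion of the first year of active treatment, patients are to have scheduled study visits every six months", and "At each visit, vital signs, clinical end points, adverse event, and concurrent medication information will be collected". Physical examination, ECG and laboratory samples are added once a year.

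Section 6.6 takes a different line on follow-up: "Regardless of their study drug status, all randomized patients should be followed for clinical end points until study completion". It also says: "Once randomized, patients should not be discontinued from study drug for noncompliance". Its provision for telephone or mail contact is addressed to patients who withdraw early from the double-blind period. For patients who stop drug prematurely, it rules out a final lipid sample that cannot be taken within 3 days of the last dose, and carries the previous value forward.

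**The concern.** A compliance condition before a lipid sample is an ordinary standardization step. Here the condition governs the whole visit. The visit is where sites routinely ask about end points, adverse events and concomitant drugs, and where scheduled safety samples are taken. If its timing depends on drug-taking, so does routine ascertainment, and drug-taking may differ between 10 mg and 80 mg. The primary log-rank comparison relies on follow-up of every randomized patient irrespective of treatment, which Section 6.6 itself calls for.

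A second, smaller issue concerns lipids. Section 9.5 reports lipid change by arm at years 1 to 5 and plans to relate events to lipid levels. If samples are taken essentially when patients are on drug, those results describe on-drug exposure, and the plan does not say so.

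**Working it through.** The plan gives no figure on this point to reproduce. The check is a side-by-side reading plus one simple ratio.

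1. **Scope.** The clause stands in the general guidelines, ahead of the subsections for screening, run-in and double-blind treatment. The sentence on fasting in the same paragraph gives a window of about 10 to 20 days that varies with study period and visit interval, so the paragraph is meant for all periods. The compliance clause has no such window.

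2. **Object.** It is the clinic visit that moves, not the blood draw. By Appendix A.1 and A.2, Visits 10, 12, 14, 16 and 18 have no laboratory tests, and neither do Visits 7 and 8. They consist of vital signs, diet counseling, dispensing, adverse events, end points and concomitant medication. Lipid standardization gives no reason to move them.

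3. **Who is caught.** Two groups remain on assigned treatment but miss the condition: patients on a temporary hold, and poor compliers, whom Section 6.6 keeps on study drug. The telephone and mail fallback in 6.6 does not expressly cover either group.

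4. **Length of delay.** Take a patient who restarts on the scheduled day and is seen two weeks later. The delay as a share of the interval is 2 weeks divided by the interval (Section 6.2.4, Appendix A.1):
   - to Visit 6 at week 12: 2/12 = 17%
   - a three-month interval in year 1, about 13 weeks: 2/13 = 15%
   - a six-month interval after year 1, about 26 weeks: 2/26 = 8%
   - the annual laboratory interval, about 52 weeks: 2/52 = 4%

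   For a patient still on hold, the delay is the rest of the hold plus two weeks, with no stated cap.

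5. **What does not wait for the visit.** Sites report potential end points within 24 hours (6.3.4). Serious adverse events and deaths are reported immediately (Appendix D, 1.2). CPK is measured within about a week while drug is held for muscle symptoms or a high CPK, and raised transaminases are repeated within about a week (6.4.1.1). Vital status is required for everyone (6.6). Event time runs to the date of occurrence (9.3.1), so an event found late keeps its date.

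6. **What does wait.** Routine questioning about end points the site has not yet heard of, non-serious adverse events, and the scheduled samples that would detect a symptomless abnormality. Read literally, the clause also covers the final annual visit (6.7). A delay there could run past the data cut-off, and Section 9.4 censors at cut-off, death or last contact.

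7. **Lipids.** Section 6.2 defers the sample until the patient is back on drug. Section 6.6 bars a sample more than 3 days after stopping and carries the earlier value forward. Both rules steer lipid data toward on-drug periods.

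**The case against.** The best defense is that the protocol never makes the visit the only route for information. Section 6.6 covers all randomized patients, the separate reporting clocks and safety visits remain in force, and complete follow-up is called critical. The compliance standard is also loose: general compliance is enough. This stands. A reader might infer that end points, adverse events or safety tests are not collected at all in these patients, but the documents do not support that.

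A reader might also infer that a persistent non-complier's visit can be put off indefinitely. The clause sets no limit, but it does not say that a rescheduled visit is postponed again. Section 6.4.1 tells sites to reinforce compliance when annual LDL is out of range, which suggests that imperfect compliers are expected to be sampled.

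Two attempts to put a size on the effect also fail:
- The Introduction gives transaminase elevations of 0.2% at 10 mg and 2.3% at 80 mg. This invites the conclusion that deferrals fall mainly on the 80 mg arm. Under 6.4.1.1, however, a confirmed elevation leads to discontinuation and follow-up under 6.6, so these rates do not count deferred visits.
- The 10% in Section 9.1 might be applied to the planned 28 mg/dl LDL difference to estimate an overstatement. That 10% is one allowance for dropout, drop-in and non-compliance combined. It is not a proportion of patients off drug under 6.2.

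Finally, on-treatment lipids are a legitimate choice of quantity. This is also right, and the criticism is only that the choice is unstated.

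**Conclusion.** The concern holds in limited form. The current text ties the timing of routine ascertainment to adherence throughout the double-blind period, without an outer limit and at visits where no sample is taken. That conflicts with Section 6.6. The consequence is later collection of routinely elicited end points, non-serious adverse events and scheduled safety samples. End-point information would be lost only if the visit did not take place before cut-off or last contact and the event reached the site by no other route.

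The effect on the primary result is probably small, and the documents do not quantify it or show its direction by arm. This rests on sites applying the clause as written and on the separate reporting rules working as intended. The lipid results by arm should be read as essentially on-drug values, though not strictly so, given the loose compliance standard and the 3-day allowance. The point merits an amendment because the correction is cheap, not because the primary comparison is shown to be biased.

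**What to change.** Reconcile Sections 6.2 and 6.6:

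- Limit compliance-based rescheduling to visits up to and including Visit 5. Visit 5 should keep the condition because its lipids form half of the baseline average (9.5).
- From Visit 6 onward, state that visits take place at the scheduled time whatever the study-drug status or compliance. End points, adverse events, concomitant therapy and safety laboratory tests are collected as scheduled, and the date of last dose is recorded.
- For lipids, choose and state one of two options. Either sample on schedule and flag drug status, amending the 3-day and carry-forward rule in 6.6 to match, or move only the lipid draw and label the lipid results as on-treatment.

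The cost is a short amendment and one CRF field, with no added visits. Under the first lipid option the reported LDL separation may be slightly smaller. The LDL action plan in 6.4.1 would also receive off-drug values, and the amendment should say how these are handled.

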### **6.2.1. Screening Visit (Visit 1)**

This single visit allows for an initial assessment of those patients the investigator feels may eventually qualify for randomization into the study. At screening an informed consent will be signed, demographic characteristics assessed, vital signs measured, all concomitant medications documented, and a medical history recorded. The investigator should screen for potential causes of secondary hyperlipidemia. These should be identified and corrected, with laboratory verification, prior to Visit 2. TSH and HbA1c measurements (for known or suspected diabetics) are obtained at Visit 1 for this purpose. Patients who appear to meet the demographic and medical history criteria should stop any prohibited medications at this visit (see section 5.3). Patients will have blood drawn for fasting lipid determinations and a standard clinical profile. LDL-C will be derived from the lipid profile (See Appendix A4 for methodology) in order to help the investigator project whether the patient will meet the inclusion criteria to enter the open-label run-in phase after dietary stabilization.

The CHD entry criteria must be documented (prior to Visit 2) through either the investigational site's medical records, or copies of such records from other institutions, or a letter from a referring physician that specifically states the diagnosis and date of the most recent occurrence of the qualifying event.

The investigator or designee will perform a general review of the patient's current dietary intake at the screening visit. The patient should receive diet information and/or other aids normally used by the site to obtain compliance with an NCEP Step I, Step II, or other equivalent diet.

The timing of Visit 2 is variable as follows. All patients previously on lipid-altering drug(s) must have these medications discontinued at the screening visit and must have at

least a 4 week washout prior to Visit 2. If the investigator is familiar with the status of the patient and is confident that the patient is already following a rigorous diet (NCEP Step I or Step II diet or equivalent) and that the patient's lipid levels are stabilized, Visit 2 (Week -8) should be scheduled either 1 week (no previous lipid therapy) or 4 weeks (on prior lipid therapy) following the initial screening visit. If the investigator is not confident that the patient is following a rigorous diet, or if this is a new patient, additional time may be needed to ensure that lipids are stabilized before randomization. In this later case, the patient should be instructed to initiate the NCEP Step I, Step II, or equivalent diet and up to 8 weeks should be allowed between the screening visit and Visit 2 (Week -8). In all cases, the screening visit must be completed no more than 8 weeks prior to entry into the open-label atorvastatin 10 mg run-in period.

If the patient has none of the screening exclusion criteria (Section 5.2.2) and has lipid levels at screening that are likely to result in entry into the active treatment phase (i.e., generally no higher than 20% above the upper limit or lower than 20% below the lower limit of the Visit 2 requirements), the patient may be entered into the open-label run-in period.

### **6.2.2 Atorvastatin 10 mg Run-In Period**

The purpose of this period is to further assess a patient's qualification for randomization based on response to atorvastatin 10 mg once daily (open-label), determine initial study medication compliance, and establish baseline values for a number of study parameters.

This period begins with Visit 2 (Week -8) and ends with randomization at Visit 5 (Week 0). Procedures for each visit are as noted in Appendix A, and Visit 2 is scheduled as noted in the prior section. Patients will be queried regarding the occurrence of adverse events and any changes or additions to concomitant medications at all open-label run-in visits.

At Visit 2, vital signs will be assessed, dietary counseling will continue and lipids will be measured. In addition, the patient will be dispensed open-label atorvastatin (10 mg) to be taken once daily. If the Visit 2 LDL-C is 130-250 mg/dl (3.4-6.5 mmol/l) and TG is  $\leq$  600 mg/dl (6.8 mmol/l) and the patient continues to have no exclusion criteria, they may be scheduled for Visit 3 (Week -4) which should occur approximately four weeks after Visit 2.

At Visit 3 (Week -4) and Visit 4 (Week -2), lipid determinations will again be made, dietary counseling will continue, and patients will continue to use open-label atorvastatin (10 mg) once daily.

Patients are eligible to return for Visit 5 if their average LDL-C (Visits 3 and 4) is  $<130$  mg/dl ( $<3.4$  mmol/l), TG  $\leq 600$  mg/dl ( $\leq 6.8$  mmol/l) at both Visits 3 and 4, and patients have been tolerant of, and compliant with, study medication at Visits 3 and 4. Visit 5 (Week 0, randomization) should be scheduled for two weeks following Visit 4.

NOTE: Patients who, after the screening visit but before randomization, experience a cardiovascular event (e.g., non-fatal MI) or develop an exclusionary condition (e.g., systemic malignancy) must be discontinued and re-evaluated for eligibility according to the timing and criteria of the screening visit (*see section 6.2.3 below*).

A summary of the pre-randomization period (Visits 1-4) along with their timing and key criteria for patient continuation is found below.

| Visit | Timing                                | Diet | Drug                          | Key Criteria for Patient Continuation                                                                                                                                                                                                                    |
|--------------|----------------------------------------------|-------------|--------------------------------------|-----------------------------------------------------------------------------------------------------------------------------------------------------------------------------------------------------------------------------------------------------------------|
| 1            | Variable (9-16 weeks prior to randomization) | Yes         | Washout                              | 
 
• Informed consent and eligible demographics/medical history
 
                                                                                                                                                  |
| 2            | Week -8                                      | Yes         | Open-label 10 mg atorvastatin begins | 
 
• LDL-C 130-250 mg/dl (3.4-6.5 mmol/l)
 
• TG <math>\leq</math> 600 mg/dl (<6.8 mmol/l)
 
                                                                                                             |
| 3            | Week -4                                      | Yes         | Continue as in V2                    |                                                                                                                                                                                                                                                                 |
| 4            | Week -2                                      | Yes         | Continue as in V2                    | 
 
• Average LDL-C <130 mg/dl (<3.4 mmol/l) from Visits 3 and 4
 
• TG <math>\leq</math> 600 mg/dl (<6.8 mmol/l) at both Visits 3 and 4)
 
• Tolerant and compliant with study medication
 
 |

#### June 13, 2003 – Amendment 4

